### Pharmacist training and support

Pharmacists will participate in mandatory training before commencing in RACFs, including an initial full-day overview of clinical pharmacy practice in the aged care setting, followed by a session focused on the pharmacist’s role in RACFs and the trial design and processes. Pharmacists will be provided with clinical and geriatric pharmacy resources including content on deprescribing, psychotropics, pain management, principles of medication review in aged care, Beers Criteria [52] and wound management.

The study team will meet face to face with pharmacists monthly to discuss potential problems and address questions. Furthermore, pharmacists will be invited to participate in quarterly meetings held by the study team to discuss study activities. An online Microsoft Teams will link on-site pharmacists to each other to facilitate a community of learning to discuss issues they are experiencing.

### Outcomes

All outcome measures will be collected from both intervention and control RACFs and compared as below.

#### Primary outcome

Change in proportion of residents who are prescribed at least one PIM (from baseline to 12 months) according to the 2019 Beers Criteria [52]

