**Methods:**

Intervention aged care facilities will employ on-site pharmacists to work as part of their healthcare teams 2 to 2.5 days per week for 12 months. On-site pharmacists, in collaboration with facility nurses, prescribers, community pharmacists, residents and families will conduct medication management activities to improve the quality use of medicines. Aged care facilities in the control group will continue usual care. The target sample size is 1188 residents from a minimum of 13 aged care facilities. The primary outcome is the appropriateness of prescribing, measured by the proportion of residents who are prescribed at least one potentially inappropriate medicine according to the 2019 Beers Criteria. Secondary outcomes include hospital and emergency department presentations, fall rates, prevalence and dose of antipsychotics and benzodiazepines, Anticholinergic Cognitive Burden Score, staff influenza vaccination rate, time spent on medication rounds, appropriateness of dose form modification and completeness of resident’s allergy and adverse drug reaction documentation. A cost-consequence and cost-effectiveness analysis will be embedded in the trial.

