### Sample size

It was estimated that a conventional RCT with randomisation of individuals would be able to detect a reduction from 60 to 40% of residents having at least one PIM [14], with a minimum of 106 residents in each arm (total of 212 residents in both arms) with a significance level of 5%, a power of 80% on equal allocation and a response rate of 85%. By adjusting for the loss of power due to clustering, with an intra-cluster correlation coefficient of 0.05 and a cluster size of 93 residents per RACF, the estimated sample size is (1 + [(93–1) x 0.05] =5.6 x 106) or 594 residents in each arm (1188 in both arms), equating to a minimum of 13 sites. The sample size was calculated using G*Power 3.1.9.4 [57].

The estimated prevalence of PIM in RACFs at baseline (60%) was based on previous studies in which the prevalence of PIM in Australian RACF residents were reported as 73% in 2018 [16], 49% in 2014 [14] and 56% in 2012 [58].

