### Statistical analysis

Descriptive statistics will be used to summarise and compare the data at the RACF level in each group at baseline and at the end of the trial, including primary and secondary outcomes as well as additional potential confounder variables (such as demographic profile, duration of residency, presence of dementia, Charlson comorbidity index [59] and number of medical conditions).

Bivariate analyses for group comparisons will use either t tests or ANOVA for data that are normally distributed, Mann-Whitney U and Kruskall-Wallis tests for data that are not normally distributed, or chi-square-based analysis for categorical outcome data. For within group comparisons, paired t tests and repeated measures ANOVAs will be used; if variables are not normally distributed, the Wilcoxon signed-ranks and Freedman tests will be used, while the McNemar test will be used for changes in proportions.

To determine the effect of the intervention on the outcome measures and the changes over time (between-within group effects), multilevel modelling methods, which take into consideration the hierarchical structure of the data (including clustering within RACF and repeated measurement occasions) will be applied. These modelling methods will include mixed-effects generalised linear models (Logistic and Poisson regression models) for binary and count outcomes as well as mixed-effects linear models for continuous outcomes assumed to have a normal distribution, or otherwise transformed to meet the assumption.

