Analysis will be weighted by cluster size as required. Interactions and adjusting for demographic characteristics and other potential covariates will be included when deemed necessary. Residents who enter, die or move from RACFs after baseline data collection will have only one data point and will be included in the analysis. When data are missing at random, patterns of missing data will be evaluated, and potential predictors of missing responses will be investigated. Methodological attempts to fill in missing data will be extensively explored and applied as appropriate. These include single imputation approaches (such as regression imputation and nearest neighbours or hot-deck imputation) and multiple imputation approaches. Analysis will be conducted using either SPSS version 26 or STATA version 16. Significance level will be set at the usual 5% alpha-level (two-tailed where applicable). All estimated effects will be reported along with their 95% confidence intervals.

Since the sample size and power calculation have been devised based on the primary outcome and hypothesis, the level of adjustment and number of potential covariates to adjust for may be limited by the sample size and the response rate. Posterior power calculations will be performed based on available sample size and the secondary outcomes.

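### The primary outcome is a change from baseline, but the trial is sized as a comparison at one time point, so the stated 80% power was not derived for the listed endpoint and use of the baseline is left open

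*Protocol article*

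**What the plan says.** The outcome is described in four places of the protocol article.

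- Abstract, Methods: appropriateness of prescribing, "measured by the proportion of residents who are prescribed at least one potentially inappropriate medicine according to the 2019 Beers Criteria". No time point is given and change is not mentioned.
- Primary outcome: "Change in proportion of residents who are prescribed at least one PIM (from baseline to 12 months".
- Sample size: an individually randomised trial of 106 residents per arm "would be able to detect a reduction from 60 to 40% of residents having at least one PIM". This is multiplied by a design effect of 5.6 to give 594 per arm, 1188 in all, from at least 13 facilities. The section describes the 60% as a baseline prevalence. It gives no correlation between the two measurement occasions and no expected 12-month rate in the control arm.
- Statistical analysis: multilevel models for the intervention effect and "the changes over time (between-within group effects", allowing for clustering by facility and for repeated occasions. Covariate adjustment is to be used where judged necessary, and residents with a single measurement stay in the analysis.

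**The concern.** A difference between arms in change from baseline and a difference between arms at one time point have different variances. How different depends on how strongly the 12-month proportion follows the baseline proportion. The article gives no value for that correlation, so a reader cannot tell what power the trial has for the endpoint it lists.

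Precision is scarce with 13 facilities, six or seven per arm. Baseline medication lists are already collected for every resident present at the start (Table 2), and how the primary contrast uses them affects precision. If the two arms' baseline means are left free and the changes are compared, the baseline is used less efficiently than it could be, and chance imbalance between a few facilities brings regression to the mean into the estimate.

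**Working it through.** **Inputs from the Sample size section:** 60% v 40%, 5% significance, 80% power, 106 per arm before clustering, intra-cluster correlation (ICC) 0.05, cluster size m = 93. The two-sided test is taken from the Statistical analysis section. **Assumed:** r, the correlation between the baseline and 12-month arm-level proportions.

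**Reproducing the plan's figure.** Two independent proportions, two-sided 5%, 80% power: 97 per arm without and 107 with continuity correction. The stated 106 is close to the second. Dividing 97 by the 85% response rate would give about 115, so the figures below leave the response rate out, as 106 appears to. Design effect: 1 + 92 x 0.05 = 5.6. Then 5.6 x 106 = 593.6, rounded to 594 per arm; 2 x 594 = 1188; 1188/93 = 12.8, so 13 facilities. The calculation is for a single time point.

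**Single-time-point power.** SE = sqrt((0.24 + 0.24) x 5.6/594) = 0.0673. Power = Phi(0.20/0.0673 - 1.96) = 84%. It exceeds 80% because no continuity correction is used here.

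**Other contrasts.** The binomial variance is 0.24 at both 60% and 40%, so equal variances on the two occasions are consistent with the plan's inputs. Relative to the single-time-point variance:

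- difference in changes, baseline means free: 2(1 - r)
- 12-month difference adjusted for baseline: 1 - r^2

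| r (assumed) | Change: variance factor | Change: power | Adjusted: variance factor | Adjusted: power |
|---|---|---|---|---|
| 0 | 2.00 | 56% | 1.00 | 84% |
| 0.3 | 1.40 | 71% | 0.91 | 88% |
| 0.4 | 1.20 | 77% | 0.84 | 90% |
| 0.5 | 1.00 | 84% | 0.75 | 93% |
| 0.7 | 0.60 | 97% | 0.51 | 99% |

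The ratio of adjusted to change variance is (1 - r^2)/(2(1 - r)) = (1 + r)/2. This is 0.65 at r = 0.3 and 0.85 at r = 0.7, a reduction of 35% and 15%.

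**What r might be.** With cluster autocorrelation CAC and subject autocorrelation SAC, r = (m x ICC x CAC + (1 - ICC) x SAC)/5.6 = (4.65 CAC + 0.95 SAC)/5.6. Illustrative values:

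- CAC 0.5, SAC 0: r = 0.42, change power 78.5%
- CAC 0.5, SAC 0.5: r = 0.50, change power 84%
- CAC 0.8, SAC 0.5: r = 0.75, change power 98.8%

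**With 85% response** (effective 0.85 x 106 = 90.1 per arm): single time point 78.2%; change 49.1% at r = 0, 78.2% at r = 0.5 and 97.2% at r = 0.75.

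**The case against.** A reader might infer that the abstract and the sample size define the outcome as a 12-month proportion and so contradict the outcome list outright. They do not. The abstract names no time point and may simply be shortened. The sample size section speaks of a reduction and calls its 60% a baseline prevalence, which is the language of change. Only its arithmetic is that of a single time point. Under randomisation, and on the risk-difference scale, both contrasts also have the same expected value; only the variance differs.

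A reader might also infer that choosing change must cost power against the sized comparison. That is not shown. It costs power only if r is below 0.5, and a moderately stable facility prevalence could put r at or above that.

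Finally, the article does not prescribe an analysis of change scores. It plans repeated-measures mixed models that keep residents with one measurement, and the details of such a model may properly sit in a fuller document.

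All of this stands, and it narrows the point. It does not supply the contrast to which the 80% belongs. A group-by-time effect with unconstrained baseline means is still a difference in changes, and the article makes adjustment discretionary, so nothing in it secures the more precise contrast.

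**Conclusion.** The listed endpoint and the power calculation do not describe the same contrast, and the 80% cannot be credited to the change from baseline. Power for a difference in changes could run from about 56% (r = 0) to 97% (r = 0.7), against 84% for the contrast that was sized. The documents neither give r nor exclude either side of 0.5, so no net loss against the sized contrast is claimed.

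What is certain, for any r from 0 up to but not including 1, is that a difference in changes with free baseline means has 2/(1 + r) times the variance of the baseline-adjusted contrast, for example 33% more at r = 0.5.

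The powers are illustrative. They use normal quantiles for about 13 clusters and a linear scale where the planned model for binary outcomes is logistic, and apart from the last line of the working they omit the 85% response rate.

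**What to change.** Use one primary contrast in the abstract, the outcome list and the analysis section: the between-arm difference in the proportion of residents with at least one PIM at 12 months, accounting for baseline. Either of two models delivers it:

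- a repeated-measures mixed model with a common baseline mean for the two arms, which keeps residents who have one data point; or
- adjustment for each facility's baseline prevalence.

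In the sample size section, state that the 80% refers to a single-time-point comparison. Because 1 - r^2 never exceeds 1, the baseline-adjusted contrast is no less precise than that comparison on the same approximation, and the sample size need not change on this account.

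The cost is wording, with no new data. The small downside is one between-facility degree of freedom if facility prevalence is a covariate: with 13 facilities in two arms, from about 13 - 2 = 11 to 10.

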#### Secondary outcomes

Rate of unplanned ED presentations and hospital admissions per resident collected from RACF records over 12 monthsPolypharmacy—number of regular medicationsChange in proportion of residents who are prescribed at least one psychotropic medicine (defined as antipsychotics and benzodiazepines), excluding those residents with major psychiatric diseases or epilepsy (from baseline to 12 months)Change in dose of psychotropic medicines (measured as chlorpromazine or diazepam equivalent daily dose [55] (from baseline to 12 months)Change in residents’ Anticholinergic Cognitive Burden Score (ACB) [56] (from baseline to 12 months)Rate of staff influenza vaccination measured at the end of influenza season, from RACF recordsFall rate per resident, as documented from RACF fall records over 12 monthsChange in time spent on medication administration rounds per RACF, through observing randomly selected medication rounds [47] (from baseline to 12 months)Change in appropriateness of medicine dose form modification per RACF, through observing randomly selected medication rounds [47] (from baseline to 12 months)Change in proportion of residents who have drug allergies or adverse drug reactions documented in their RACF records (from baseline to 12 months)Number of medication-related incidents over 12 monthsCost-consequence and cost-effectiveness of the intervention over 12 months

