Integrating an on-site pharmacist as part of the RACF health care team may address the gap in provision of medication management practices, policies and processes. On-site pharmacists, in collaboration with nurses, GPs, specialists, community pharmacists, residents and families will conduct medication management activities to improve the quality use of medicines at the facility [47–50]. This new model can improve communication among the healthcare team and enhance resident and family’s involvement in medication management decisions for individuals [48], leading to improved person-centred care. At the facility level, the on-site pharmacist can develop and enhance RACF policies and procedures for overall medication management [44]. These system improvement activities include reviewing and enhancing medication ordering, storage and administration processes, as well as conducting staff education, providing medication information, responding to medication utilisation reports, developing clinical referral pathways and contributing to staff and resident influenza vaccination.

A proposed model of integrated on-site pharmacist services into the RACF health care team was examined in a pilot study which was conducted by the lead author [47–51]. The conceptual foundation of the new model was to improve multi-disciplinary care, communication and collaboration in RACF’s healthcare team to enhance medication management [47, 48]. The findings of the pilot study indicated that the integration of a pharmacist into a RACF was feasible and acceptable to RACF staff, residents and GPs and resulted in improved medication administration and clinical documentation [47], increased provision of education for nursing and carer staff to promote the quality use of medicines and prevent medication administration errors [48], and enhanced staff influenza vaccination rates [49]. The positive findings of the pilot study informed the allocation of program funds from the Australian Department of Health to implement and evaluate this model in RACFs in the Australian Capital Territory (ACT).

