#### Pharmacists

Qualified pharmacists will be recruited through open expressions of interest sent to pharmacy professional groups and associations. The selection criteria for pharmacists include having registration with the Australian Health Practitioner Regulation Agency, accreditation to conduct medication reviews by the Australian Association of Consultant Pharmacy or equivalent hospital or geriatric clinical pharmacy experience, and accreditation to conduct vaccination. A list of eligible pharmacists will be provided to the intervention RACFs, who will employ pharmacists as per their organisational policy. Salaries for pharmacists will be funded by the research grant; however, they will be directly employed by RACFs as RACF staff members.

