Performing medication reviews in collaboration with residents, families, prescribers and nursesIdentifying residents at high risk of medication-related harm and hospitalisation, and prioritising interventions to address themMedication reconciliation and review at transition of careParticipating in case conferences with GPs, palliative care team, families and residentsReviewing and optimising medication administration roundsUpdating and improving resident records including clinical and care informationAnswering medication-related queries from residents, families and staffConducting regular clinical audits to identify medication-related problemsEducating residents, families and RACF staff about medication-related issuesImproving the RACF’s medication management policies and proceduresParticipating in relevant RACF committees and meetings including Medication Advisory Committee, Quality and Safety meetings, Falls Review Committee, and Medication Incidents Review CommitteeImproving influenza vaccination rates of staff and residents

Pharmacists in intervention sites will not be permitted to conduct RMMR or QUM services. RACFs will receive these services from existing providers as a part of usual care.

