**Facility level data**	
Number of permanent residents, proportion of residents with dementia, and proportion receiving the highest level of government funding	Baseline and at 12 months
Number of RACF registered nurses rostered during day/night/weekend	Baseline and at 12 months
Care staff turn-over reported by RACFs	Baseline
Total number of beds and bed occupancy rate	Baseline
Resident turn over	Monthly
Number of medication-related incidents	Monthly
Number of resident falls	Monthly
Time taken to conduct medication rounds	Baseline and at 12 months
% of staff/residents received influenza vaccination	At one time point
% of residents that have drug allergy and adverse drug reactions documented	Baseline and at 12 months
Number of GPs visiting residents in facility	Baseline
RACF managers perceived top 5 reasons for unplanned hospitalisations of residents in previous 12 months, and possible solutions for reducing these	Baseline

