**Resident level data**	
Age and gender	Baseline
Date of admission and discharge and reason for discharge from the facility	Baseline and monthly
Diagnosis	Baseline and at 12 months
Number and list of regular and PRN medications including dosages	Baseline and at 12 months
Emergency Department visit/transfer*	Baseline and monthly
Hospital admissions* and length of hospital stay as determined by RACF residents’ records	Baseline and monthly
Reason for Emergency Department visit/admission to hospital - as determined by RACF residents’ records	Baseline and monthly

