The study is using a staggered approach to the recruitment and intervention. Due to the impact of the recent COVID-19 pandemic on RACF’s workforce and operations, this staggering will provide the facilities with time to prepare and adapt to recent policy and procedural changes. These changes may impact on the study outcomes; for example, there may be changes in the number of regular healthcare staff in RACFs or residents may receive fewer GP and other visiting healthcare professional visits and this may impact the level of collaboration with pharmacists. Potential restrictions in visiting RACFs due to COVID-19 pandemic may affect the data collection processes. On-site pharmacists participating in this study will have accreditation to conduct medication review; however, they may be at different level of experience and skills, which may impact the quality of pharmacist activities in some RACFs. This will be further explored by assessing the fidelity of interventions that determines whether the intervention was conducted as planned across the intervention RACFs and includes an audit on the appropriateness of pharmacists’ medication reviews. Participating RACFs will be all within ACT which is a metropolitan area in Australia; thus, the findings may not be generalisable to RACFs located in rural and remote areas.

A number of limitations should be noted. PIMs are a proxy measure for appropriateness of prescribing, which represents an ideal level of care and is reliable in predicting adverse events [62]. The study does not include measurements of resident focused indicators such as Quality of Life, noting the difficulties in seeing changes in elderly frail population. The reporting of secondary outcomes is based on facility records, which may be under reported.

The study provides important information on clinical and economical outcomes of the model where on-site pharmacists are integrated into RACFs’ health care team to improve medication management. The results will provide policymakers with recommendations relevant to the potential further implementation of this model.

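### The medication-incident count depends on facility reporting that the intervention may itself change, so a difference between arms cannot be read as benefit or harm on its own

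*Protocol article*

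**What the plan says.** The Secondary outcomes section includes "Number of medication-related incidents over 12" months and a fall rate per resident taken from facility fall records. The Outcomes section says that all outcome measures are collected in both groups and compared. In Table 2, under facility level data, "Number of medication-related incidents" and "Number of resident falls" are both collected monthly, and no baseline collection is listed for either. ED visits, hospital admissions and the reasons for them are listed at baseline and monthly.

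The Intervention and model of care section gives the intervention pharmacist, among other duties, audits to find medication-related problems, staff education, improvement of resident records and of medication policies, and membership of committees including "Quality and Safety meetings, Falls Review Committee, and Medication Incidents Review" committee. The Pharmacists section adds that "they will be directly employed by RACFs as RACF staff members". The Background reports that the pilot "resulted in improved medication administration and clinical documentation".

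Under Randomisation and blinding, trial participants are not blinded. The Discussion states the limitation: "The reporting of secondary outcomes is based on facility records, which may be under reported".

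**The concern.** A count of reported incidents is the product of two things: how many incidents occur and what share of them is written down. The trial wants to learn about the first. Several of the pharmacist's duties, present in one arm only, could plausibly change the second. Auditing brings problems to light, education teaches staff what to report, and committee work draws attention to the reports. The pilot's finding on clinical documentation shows that a change in recording is not far-fetched.

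Under-reporting that is equal in both arms cancels out of a rate ratio. Under-reporting that differs by arm does not, and the Discussion's limitation does not make that distinction. The mixed models and covariate adjustment in the Statistical analysis section cannot remove a reporting difference that coincides with treatment arm.

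At stake is how one secondary outcome, and to a lesser degree the fall rate, is read. The cost-consequence analysis will put the secondary outcomes before decision makers. A gain in reporting could be taken there for a rise in incidents, or could conceal a real fall in them.

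**Working it through.** The protocol gives no expected rate, effect size or power for incidents or falls, so there is no figure of its own to reproduce. The check has two parts.

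**1. Does the intervention touch the source of the outcome?**

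- Medication incidents: the source is a facility-level count. The pharmacist is facility staff, audits for medication-related problems, educates staff, improves medication procedures and sits on the committee that reviews these incidents. The links are several and fairly direct.
- Falls: the source is facility fall records. The links are membership of the falls committee and general improvement of resident records. They are fewer and less direct.
- Separation of recording from occurrence: for these two counts the article describes no independent ascertainment and no restriction by severity. Table 2 lists no baseline count, so a reporting difference that already existed between facilities could not be told apart from one caused by the intervention. The planned minimum is 13 sites.

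**2. How much could it matter?**

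Let s0 and s1 be the shares of true incidents recorded in the control and intervention arms. Then

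observed rate ratio = true rate ratio × (s1 / s0).

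The documents give neither share. The values below are assumptions: s0 from 0.5 to 0.7, and s1 from s0 up to 0.9.

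| True ratio | s0 | s1 = 0.5 | s1 = 0.6 | s1 = 0.7 | s1 = 0.8 | s1 = 0.9 |
|---|---|---|---|---|---|---|
| 1.00 | 0.5 | 1.00 | 1.20 | 1.40 | 1.60 | 1.80 |
| 1.00 | 0.6 | – | 1.00 | 1.17 | 1.33 | 1.50 |
| 1.00 | 0.7 | – | – | 1.00 | 1.14 | 1.29 |
| 0.80 | 0.5 | 0.80 | 0.96 | 1.12 | 1.28 | 1.44 |
| 0.80 | 0.6 | – | 0.80 | 0.93 | 1.07 | 1.20 |
| 0.80 | 0.7 | – | – | 0.80 | 0.91 | 1.03 |

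For example, 0.80 × 0.9 / 0.5 = 1.44, and 0.80 × 0.8 / 0.6 = 1.07.

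The point at which a true reduction vanishes needs no assumed completeness, only the true ratio. For a 20% reduction, s1 / s0 = 1 / 0.80 = 1.25.

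The formula also works the other way. If reporting became less complete in the intervention arm, say s1 / s0 = 0.8, then no true effect would appear as 1.00 × 0.8 = 0.80, a spurious benefit.

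**The case against.** The strongest reply is that the effect on reporting is inferred. No section says that the pharmacist is there to improve incident or fall reporting. Committees review events already reported, and a medication-related problem found on audit is not shown to become a recorded incident. The completeness figures are assumed, and the arithmetic only carries the assumption forward. The research team normally visits to collect outcome data, and the protocol already names reliance on facility records as a limitation. All of this stands. It limits the point to a risk that the plan does not address. It does not remove the point, because research visits retrieve only what the facility recorded, and the stated limitation does not mention a difference between arms.

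Four stronger readings are tempting, and the documents do not support them:

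- **That the bias runs in one direction.** More recording is the more plausible result, but an on-site pharmacist could also settle errors informally, with no report filed.
- **That a rise in recorded incidents could stop the trial.** The Safety evaluation and reporting section relies on an adverse event log, with external clinical consultants assessing causality and seriousness. It does not name the incident count as a trigger.
- **That falls are affected as strongly as incidents.** The links are weaker, and nothing says that a part-time pharmacist changes whether a fall is logged.
- **That falls leading to hospital contact should replace the fall rate.** "Reason for Emergency Department visit/admission to hospital" is also determined from facility records, and the pharmacist's work with residents at high risk of hospitalisation could affect transfers themselves.

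**Conclusion.** The concern holds as a minor point of interpretation, chiefly for the medication-incident count. As planned, a difference between arms in that count could reflect recording, occurrence or both, and nothing described in the article tells them apart. If recording is a quarter more complete in the intervention arm, a true 20% reduction is hidden. Over the assumed range, a true 0.80 is seen as 0.80 to 1.44. These sizes rest on assumed completeness and on recording being no worse with the intervention than without it. The documents settle neither. For falls the concern is weaker. The primary outcome, which rests on medication lists, is not affected.

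**What to change.** 1. Present the medication-incident count as a process (reporting) measure, expressed per resident-month, and draw no conclusion of benefit or harm from it alone. Monthly counts, resident turnover and admission and discharge dates are already in Table 2.
2. Keep the fall rate as the stated outcome. Add, as a supporting analysis, the rate of falls leading to an ED presentation or hospital admission, using the reason field that Table 2 already collects at baseline and monthly.
3. Extend the limitation in the Discussion to say that completeness of reporting may differ by arm because of the intervention.

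The cost is some wording and one extra analysis of data already collected. The restricted fall analysis will have fewer events. Its reason field comes from facility records too, so the bias is reduced and not removed. The trial also gives up an effectiveness claim on incidents taken from the count alone.
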